### Recruitment

Because married women are included in the surveillance system established by the Department of Pediatrics and Child Health at the Aga University, VITAL Pakistan Trust has access to a list of all the pregnant women in the catchment area. Using that list, all households with pregnant women will be visited by the research team to offer standard ANC services. Thereby, during each pregnancy milestone, antenatal and nutritional counseling will be provided about optimal care-seeking approaches. At the time of clinical ANC visit for delivery, these women will be reapproached by the randomization/enrollment team so that their eligibility is assessed for the trial.

### Informed consent procedure

Eligible pregnant women fulfilling the predefined inclusion criteria will be explicitly explained the aims of the study, procedures and duration of the enrollment. In a household where decision-makers are either husbands or other senior family members (not a woman independently), permission from those decision-makers will be sought to avoid loss to follow-up at a later stage. Adequate time will be given to each participant, i.e., 24–48 h, for discussion with the family members to avoid dropouts and non-compliance. Consent for study participation will be obtained by the research assistant in the presence of a community health worker. To ensure comprehension of the trial and study procedures, clear verbal communication in the study participant’s native language will be imparted. Uneducated participants will be asked to give a thumb impression on the consent form; literate guardians will be requested to sign the consent form.

### Randomization and allocation concealment

After written informed consent is obtained, randomization will be performed by the team. Stratified block randomization with blocks of sizes 4, 8, and 12 will be used. Sequence generation will be performed by an independent statistician using a random selection method before the beginning of the trial. Self-adhesive, pre-coded sticky labels with unique identification numbers will be applied to sealed opaque envelopes containing the coded randomization identification number and intervention name to ensure that the randomization process and allocation are blinded. Baseline information regarding nutrition and exclusive breastfeeding will be recorded. Anthropometric measurements of both the mother and newborn will be performed, and follow-up procedures will be explained. Figure 1 shows the trial processes in detail.

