### Sample size

The sample size is calculated via permutation and subsequent adjustment for three comparisons between arms, i.e., intervention arms with control. Improved perinatal outcomes are hypothesized with the supplement of BEP alone or co-administration of BEP supplement with azithromycin as well as with nicotinamide and choline. Thus, the sample size estimated per arm is based on 1-tailed hypothesis testing of birth weight as the primary outcome, a significance level of 2.5% to account for multiple comparisons, and initial assumption of dropout proportion of 21% of study participants assumed in the trial. For birth weight (the primary outcome), it is assumed that the mean difference will be at least 100 g [30]. In order to achieve a test power of 80% and maintain family-wise error rate (FWER) of 0.05; Bonferroni method for three comparisons, alpha of 0.017, and an estimated sample size of 370 pregnant women per arm was attained. A 21% dropout rate was thereafter considered on account of miscarriages, stillbirths, early neonatal deaths, losses to follow-ups, and missed birth assessments due to varying on-field challenges owing to the pandemic. Hence, the sample size was thereafter adjusted to 471 pregnant women in each arm making up a total of 1884 pregnant women for this trial.

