### Primary outcome

The primary outcome of interest will be the birth weight (g) of the newborn assessed within 72 h of birth.

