### Statistical analysis

All analyses will be done using Stata software version 16. Descriptive analysis of each group will be conducted, and percentages or continuous data with SD will be reported. The baseline characteristics will be assessed by arm. The primary approach will be intention-to-treat (ITT) analysis to compare primary and secondary growth outcomes. Mean differences will be assessed using one-way ANOVA, with the model adjusted for baseline characteristics including maternal age, BMI, gestational age, gravidity, MUAC, and newborn age at birth assessment. Key assumptions are that outcome data will be repeatedly measured, normally distributed, and following the superiority principle. For covariate analysis, both the unadjusted and stepwise-adjusted models will be run. Point estimates less than 10% will be reported as unadjusted despite of the model employed. Potential sub-group analyses for primary and secondary outcomes will be based on infantile gender and maternal data at enrolment, i.e., MUAC < 21.0 cm or ≥ 21.0 cm, age < 30 years or ≥ 30 years, gravidity < 3 or ≥ 3, and BMI < 18.5 kg/m^2^ or ≥ 18.5 kg/m^2^.

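### Randomisation is stratified, but the analysis section does not tie the model to the strata, and its model-choice rules can leave them out of the reported result

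*Protocol article*

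**What the plan says.** In the protocol article, the Randomization and allocation concealment section states: "Stratified block randomization with blocks of sizes 4, 8, and 12 will be used". Neither that section nor any other names the factor or factors that define the strata.

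The Statistical analysis section plans a one-way ANOVA of mean differences, "with the model adjusted for baseline characteristics including maternal age, BMI, gestational age, gravidity, MUAC, and newborn age at birth assessment". The randomisation strata are not mentioned as such. Two further sentences govern which model is run and reported: "For covariate analysis, both the unadjusted and stepwise-adjusted models will be run" and "Point estimates less than 10% will be reported as unadjusted despite of the model employed".

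The primary outcome is continuous: "The primary outcome of interest will be the birth weight (g) of the newborn assessed within 72 h of birth". For the sample size, "the sample size estimated per arm is based on 1-tailed hypothesis testing of birth weight as the primary outcome". That section gives two significance levels. One is "a significance level of 2.5% to account for multiple comparisons"; the other comes with the per-arm number: "Bonferroni method for three comparisons, alpha of 0.017, and an estimated sample size of 370 pregnant women per arm was attained".

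**The concern.** Blocking within strata forces the arms to be nearly balanced on the stratification factors. If those factors predict birth weight, the design removes between-stratum variance from the comparison of arms. A model without the strata still counts that variance as error, so its standard error exceeds the true sampling error of the difference. Intervals are then wider than the design warrants and tests reject less often than their nominal level.

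The article fixes more than a covariate list; it also fixes rules for choosing the reported model, and those rules do not protect the strata:

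- The unadjusted model excludes them by construction.
- Stepwise selection can drop a listed covariate on the data.
- The 10% sentence is unclear. Its natural reading is a change-in-estimate rule: if adjustment moves the estimate by less than 10%, the unadjusted result is reported. Because stratified allocation balances the strata across arms, adjusting for them should barely move the estimate; what it changes is the standard error. Such a rule therefore tends to discard the very variables that stratification has balanced, whichever factors were used.

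At stake are precision and a clear match between design and analysis. Bias is not at issue.

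**Working it through.** **Inputs from the article (Sample size section):** difference 100 g; power 80%; one-tailed test; alpha 0.017 (Bonferroni, three comparisons); 370 per arm before dropout; 21% dropout; 471 per arm and 1884 in total.

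**Assumed, because not in the article:** the SD, and R², the share of variance not otherwise adjusted for that the strata explain.

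**Step 1: the plan's own figures.** No SD is given, so 370 per arm can be neither confirmed nor refuted. Solving n = 2·SD²·(z_alpha + z_power)²/100² for SD:

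- one-sided 0.017: SD = 100·√(370/2)/(2.120 + 0.842) = 459 g
- one-sided 0.025: 485 g
- two-sided 0.017: 421 g

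The dropout step reproduces closely: 370/(1 − 0.21) = 469 against the stated 471, and 4 × 471 = 1884. I carry forward 459 g, which matches the stated one-tailed test at 0.017.

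**Step 2: standard errors.** A model without strata reports SE = 459.2·√(2/370) = 33.76 g. The true standard error under stratified allocation is SE_true = 33.76·√(1 − R²).

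**Step 3: power and actual alpha.**

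- With strata: power = Φ(100/SE_true − 2.120)
- Without strata: power = Φ((100 − 2.120·33.76)/SE_true)
- Actual one-sided alpha without strata: 1 − Φ(2.120·33.76/SE_true)

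| R² (assumed) | SE_true (g) | Reported SE too wide by | Power with strata | Power without | Difference (points) | Actual alpha without |
|---|---|---|---|---|---|---|
| 0 | 33.76 | 0% | 80.0% | 80.0% | 0 | 0.0170 |
| 0.02 | 33.43 | 1.0% | 80.8% | 80.2% | 0.6 | 0.0161 |
| 0.05 | 32.91 | 2.6% | 82.1% | 80.6% | 1.5 | 0.0148 |
| 0.10 | 32.03 | 5.4% | 84.2% | 81.3% | 2.9 | 0.0127 |

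Power without strata also rises with R², because the design itself reduces the sampling error. The cost of leaving the strata out is therefore the gap between the two power columns. Comparing 84.2% with a flat 80% would put it at 4.2 points instead of 2.9.

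**Step 4: sensitivity to the alpha statement.** At one-sided 0.025 with its implied SD and R² = 0.10, power with strata is Φ((1.960 + 0.842)/√0.90 − 1.960) = Φ(0.993) = 84.0%. Without strata it is Φ(0.842/√0.90) = 81.3%. The gap is about 2.7 points, so the choice between the two stated levels hardly matters here.

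**The case against.** The strongest reply is that omission of the strata is not shown. The factors are unnamed, and the covariate list is introduced by *including*, so it is open. The trial has a single setting, so no centre stratum is evident. A maternal baseline factor such as MUAC, gestational age, gravidity, age or BMI would already be on the list. If so, and if the adjusted model is the one reported, nothing is lost. This stands. A reader might infer that the planned model definitely omits the strata, that its standard errors are too wide and that power is thrown away; the article does not support that as an unconditional statement.

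A second reply is that placing stratification factors in the model is ordinary content for a statistical analysis plan, which is not shown here. That would be decisive if the article were merely silent. But the article states a model, a selection method and a reporting rule, and even a listed factor may not survive them into the reported result. The 10% sentence is garbled, and my reading of it is the natural one, not the only one.

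A third reply is that the consequence is benign. This also stands: the error is conservative, and the sample size takes no credit for stratification. The relevant R² is also only what the strata explain beyond the covariates in the reported model, which may be small.

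**Conclusion.** The point holds in a limited form. The article commits to stratified randomisation but does not connect the analysis to the strata, and its unadjusted model, stepwise selection and 10% rule can yield a reported result that ignores them. If the strata predict birth weight beyond the covariates in that result, the cost is about 0.6, 1.5 or 2.9 power points at R² of 2%, 5% or 10%. Standard errors are then 1.0%, 2.6% or 5.4% too wide, and actual one-sided alpha at R² of 5% or 10% is 0.0148 or 0.0127 against 0.017.

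These sizes rest on an assumed R² and an SD back-solved from 370 per arm. The loss is zero if the strata are not prognostic or are already in the reported model. Power stays at or above the planned 80% in every scenario shown, and type I error is not inflated. What may be forgone is a modest gain in precision.

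**What to change.** In the randomisation section, name the stratification factor or factors.

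In the Statistical analysis section, add wording such as: *All models for primary and secondary outcomes include the randomisation stratification factor(s) as fixed effects, including the model described as unadjusted. These factors are not subject to stepwise selection or to the 10% reporting rule.* If the full protocol or analysis plan already says this, the article's text should be brought into line with it.

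The change should be made before the allocation code is revealed; the Trial status section puts the database lock in June 2024. It needs no new data, since the strata are already on the allocation list. It uses a few degrees of freedom out of about 1480 (4 × 370).

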**Fig. 1 Fig1:**
[figure not shown]
Consort diagram

### Blinding

The outcome assessors, responsible only for the anthropometry measurements, will be blinded and assigned a schedule that does not overlap with those of the follow-up teams. All investigators will also be blinded to group allocation throughout the period of the study. Moreover, an interim analysis on the blinded arms will be executed by an independent statistician for the Data Safety and Monitoring Board (DSMB). Furthermore, the data analyst performing the final analysis will also be blinded, and the code will eventually be revealed after the blinded results will be shared with DSMB and investigators in a final review meeting.

### Interventions

In the control arm, standard of care, i.e., ANC care, nutritional counseling, health promotional messages of exclusive breastfeeding, and care for intrapartum and postnatal care will be disseminated to all pregnant women. In “Intervention arm 1,” in addition to the standard of care, 2 sachets of BEP supplements per day from enrolment till birth outcome will be allocated to each woman by a trained research team member at initial and subsequent follow-up visits. BEP is a certified product of the World Food Program and is locally produced by the Ismail Industries in Karachi. The manufacturers have no role in any part of the study. Each sachet contains a caloric value of 400 kcal per 75 g and approximately 10.5 g of protein. The sources of protein are mainly chickpea, peanuts, lentils, legumes, and skimmed milk. In “Intervention arm 2,” the same standard ANC counseling BEP interventional doses will be administered to each participant in addition to 2 prophylactic doses of azithromycin tablets 2 g orally at weeks 20 and 28 of gestation (window period of 7 days). In “Intervention arm 3” lastly, daily single doses of nicotinamide 100 mg orally and choline 450 mg orally will be dispensed to each pregnant woman in addition to the same standard of care plus BEP diet supplements. Provision of all ANC services as well as referral for any complication(s) during pregnancy and intrapartum period will be undertaken for all arms. Provision of all ANC services as well as referral for any complication(s) during pregnancy and intrapartum period will be undertaken for all arms. There will be no alternation to the usual care pathways (including use of any medication) and these will continue for all trial arms. All other non-study treatments, such as medications and supplements, will be recorded at each follow-up in all arms. In case any severe illness or adverse event is reported or observed, the intervention may be paused or stopped for a limited period after the investigators and the Data Safety and Monitoring Board are consulted.

### Data collection and data management

Case report forms (CRFs) are designed to capture details on screening, eligibility, randomization, household demography, pregnant assessment, danger signs, severe adverse events, interventional compliance, 24-h food recall (to estimate usual intake plus diversity on a monthly basis), and anthropometry. The data will be collected by a trained team on electronic tablets, with intrinsic logic checks and skip patterns, and updated on secure servers in real time using digital applications, which are designed and built in-house. Auto-alerts will be used to remind about each participant’s follow-up as per schedule, and the data will be tracked according to key indicators. All the data will be collected in a real-time manner and uploaded on a cloud server, which is password-protected and only accessible to the trial data management team and manager. Participants’ confidentiality will be maintained through a unique ID system, and the participant identification information will not be exposed to anyone outside the trial team. The tablets in use will be password-protected and only accessible to the study team. De-identified data will be used for analysis purposes.

### Follow-ups

Domestic visits will be paid by the follow-up teams to provide counseling for all arms. BEP will also be provided to all intervention arms, and compliance will be measured by logging the number of empty sachets since the last visit. Azithromycin oral dose (intervention arm 2) will be given to pregnant women by the research team with close monitoring of adverse events if reported or observed. Similarly, daily administration of nicotinamide and choline will also be the responsibility of the designated follow-up team (intervention arm 3). Follow-ups will be performed daily for the first 15 days following enrollment, every 72 h in the following 2 weeks, and, then weekly in the next stages of pregnancy till birth outcome. At each visit, counseling will be provided to the participants to reinforce adherence to the BEP supplementation and other protocol-related procedures. In addition, monthly 24-h food recall data will also be collected. After birth outcome assessment, the mother-infant dyad will be followed through 0–11 months of infant’s age on a periodic basis. There is no plan of retention for these participants once their 11-month follow-ups are completed. However, through our existing free-of-cost primary health care facilities, standard-of-care is available to all participants, even after the completion of the trial. For participants who move out of the catchment area, a tracking system has been developed so that they can be followed up at the new location in case it is in close proximity. Table 2 shows the schedule of enrollment, interventions, and assessments.

**Table 2 Tab2:** Time schedule of enrollment, interventions, and assessments

Timepoints	T_**0**_^**a**^	Follow-ups collecting data on key study variables and indicators					Follow-ups for maternal anthropometry	Week 19	Week 32	Primary study endpoint	Extended follow-up Mother-infant dyad (Secondary study end points)
		Daily visits^b^	48 hourly visits ^c^	72 hourly visits ^d^	Daily visits^e^	Weekly^f^	Week 23, 27, 31, 35, 39 of gestation				
										At birth	1–2 months, 3–4 months, 5–6 months and 12 months
**Enrollment**											
*Eligibility assessment*	×										
*Written informed consent*	×										
*Randomization and allocation*	×										
*Baseline data*	×										
**Intervention**											
*Nutrition counseling and ANC*	×	×	×	×	×	×					
*BEP distribution and compliance assessment* ^*g*^	×	×	×	×	×	×					
*Oral Azithromycin administration at week 20 and 28 with daily follow-ups for SAEs monitoring after dose administration* ^*h*^					×						
**Follow-ups during pregnancy**											
*24 h breastfeeding recall*			×	×	×	×					
*Infant assessment for danger sign*			×	×	×	×					
*24 h maternal food intake recall* ^*i*^						×					
*Monthly maternal anthropometry measurements performed by separate team (blinded from intervention details)*							×				×
*Maternal depression*							×	×			
*Participant experience and rating different characteristics of BEP product* ^*g*^							×	×			
**Specimens’ collection during pregnancy**											
*Maternal hemoglobin level* ^*j*^	×								×		
*Maternal ferritin level* ^*j*^	×								×		
*Maternal vitamin D level* ^*j*^	×								×		
*Maternal VAM blood collection* ^*j*^	×								×		
*Maternal urine collection for Choline metabolites* ^*k*^	×								×		
*Maternal plasma collection for proteomics* ^*k*^								×	×		
*Maternal plasma collection for Niacin metabolites* ^*k*^								×	×		
*Maternal stool collection*											
**Birth outcome assessment**											
*Newborn and maternal anthropometry measurements within 72 h of birth performed by separate team (blinded from intervention details)*										×	
**Specimens’ collection soon after birth**											
*Cord blood collection within 30 min of birth* ^*k*^										×	
*Breast milk collection within 72 h of birth* ^*k*^										×	
**Specimens’ collection during extended follow-up**											
*Mother-infant dyad VAM blood collection* ^*k*^											×
*Mother-infant dyad stool collection* ^*k*^											×
**Infant’s growth and neurodevelopment assessment**											
*Monthly infant and maternal anthropometry measurements performed by separate team (blinded from intervention details)*											×
*Neurodevelopment assessment using Mullen, HINE and GSED – at 6 and 12 months of infant’s age plus maternal depression* ^*l*^											×
*MRI scan of infants* ^*k*^											

^a^Window period for eligibility assessment and enrollment is 8–18.9 weeks of gestation

^b^Initial 1–13 days from enrollment

^c^15–25 days from enrollment

^d^29–38 days from enrollment

^e^Pre- and post-Azithromycin administration, i.e., at weeks 20 and 28 of gestation

^f^48 days from enrollment

^g^Only in intervention arm

^h^Only in intervention arm C and window period of 7 days

^i^Only monthly basis

^j^All participants who agreed

^k^Sub-sample of 50 in each arm

### Anthropometry

The teams will be trained to perform anthropometric measurements for each mother-infant dyad using the INTERGROWTH-21st standards by a master trainer who will also conduct monthly refreshers. The measurements will include maternal height, mid-upper arm circumference (MUAC), and weight as well as infant length, weight, MUAC, and head circumference. SECA infant weighing scale model 334 will be used for infantile weight measurement whereas the SECA adult weighing scale model 874 will be used to assess the maternal weight. MUAC tapes from UNICEF will be imported. The SECA scale models 417 and 213 will be used to measure the maternal height and infantile length respectively. The team members recording anthropometric measurements will be blinded to the allocated arms of participants. Data will be entered digitally in the system which will automatically calculate the average value. The allowable difference between the two study measurements according to the standard procedure is ± 0.5 cm for maternal MUAC, ± 0.2 kg for maternal weight, ± 0.5 cm for maternal height, ± 20 g for infant weight, and ± 0.4 cm for infant length, infant MUAC, and infant head circumference.

### Primary outcome

The primary outcome of interest will be the birth weight (g) of the newborn assessed within 72 h of birth.

### Secondary outcomes

The other outcomes of interest will be birth length (cm), head circumference (cm), and MUAC (cm) of the newborn assessed in less than 72 h of birth. For extended follow-ups on days 3, 6, 21, 27, 42, 59, 89, 114, 143, 179, 269, and 359 from 0 to 11 months after birth, anthropometry of the mother-infant dyad will be assessed. Weight velocity (g/day), length velocity (cm/month), length-for-age *z*-score (LAZ), weight-for-age *z*-score (WAZ), and weight-for-length *z*-score (WLZ) will thereafter be calculated. Weight velocity is defined as the incremental change in weight (in grams) per day from birth to 11 months of age. Similarly, length velocity is defined as the progressive change in length (in centimeters) per month measured from birth to 11 months of infantile age. Moreover, the mean differences in the specific *z*-score indicators (LAZ, WAZ, and WLZ) measured at birth and 11 months of age will be assessed. Because anthropometric data for each mother-infant dyad is available on different periodic days as per their follow-up schedule, the aforementioned outcomes assessed according to each follow-up’s duration. Furthermore, the anthropometric measurements of the mother will also be assessed on a monthly basis during pregnancy, i.e., height (cm) (only at enrollment), weight (kg), and MUAC (cm), and body mass index (BMI). The mean change in each of these indicators for different arms will be assessed during pregnancy and in extended postnatal follow-ups.

